### Outcome Measures

#### Sleep

The primary outcome is TST, with secondary outcomes of sleep onset, WASO, shuteye latency, sleep onset latency, sleep disturbances, and sleep impairment assessed using objective and subjective measures (Figure 2). AX3 accelerometers will be worn on the nondominant wrist, 24 hours a day, for 7 days during the baseline week and 3 days during intervention weeks 2-5. These accelerometers provide accurate measures of our sleep variables in this age group, as determined against the gold standard polysomnography [67]. These devices are smaller than a watch, waterproof, unobtrusive, and do not need to be removed for sport or bathing, ensuring high wear time compliance rates [68]. After initialization of the accelerometer, the data will be downloaded with OmGui software (version 1.0.0.30; Open Movement), saved in raw format as .cwa files, then converted into ActiGraph counts for data processing [69]. Sleep variables are obtained using an automated script developed in MATLAB (MathWorks) that uses a count-scaled algorithm to estimate sleep and wake epochs for each individual for each day [70]. Sleep onset is then determined as the start of the first 15 continuous minutes of sleep preceded by 5 minutes of awake. Sleep offset is determined as the last of 15 continuous minutes of sleep followed by 5 minutes of awake. WASO is determined as the number of minutes from the sum of all movement epochs that occur over 5 continuous minutes of awake between sleep onset to offset. TST is determined as the number of minutes from sleep onset to sleep offset minus WASO. The remaining sleep variables of interest will be measured from the stationary video data. Bedtime is determined as the first time the participant gets into bed and under the covers. Shuteye time is determined as the first time the participant stops interacting with any device or person and appears to close their eyes to try and go to sleep. Shuteye latency is calculated as the difference between bedtime and the first shuteye time. Sleep latency is calculated as the difference between shuteye time from the video camera data until sleep onset time from the accelerometer. Sleep disturbances (difficulties falling and staying asleep) and sleep impairment (daytime alertness and sleepiness) will be measured using 2, 8-item PROMIS (Patient-Reported Outcomes Measurement Information System) questionnaires [71]. The questionnaires were originally designed with a 7-day recall and will be used in this context to assess usual sleep disturbances and impairment during the baseline week on day 8 (therefore covering the previous week). An adapted version assessing the previous night only, will be used to measure sleep disturbances on the previous night and will be administered on the morning of days 6, 7, and 8 of each intervention week, asking about “Last night…” rather than “Over the past 7 days.” An adapted version assessing sleep impairment over the previous 3 days will be administered on the evening of day 8 of each intervention week, with the anchors for these questions changing from “Over the past 7 days” to “Over the past 3 days.”

**Figure 2 figure2:**
[figure not shown]
Outline of the measurement schedule. PROMIS: Patient-Reported Outcomes Measurement Information System.

#### Health-Related Quality of Life

Participants will complete the 10-item KIDSCREEN questionnaire that assesses health-related quality of life over the past week [72] at the end of the baseline week. As with the PROMIS impairment questionnaire, an adapted version of the KIDSCREEN questionnaire will be completed in the afternoon of day 8 of each intervention week. The adapted version changes the answer anchors from “Thinking about the last week...” to “Thinking about the last 3 days...”

#### Participant and Family Experiences

At the end of each intervention week, participants and families will provide brief feedback on their experiences, rating the ease of activity on a scale of 1 to 5, and providing reasons for their rating. In addition, 16 participants and families will take part in semistructured interviews upon study completion, offering detailed qualitative feedback on each intervention activity, its feasibility for integration into daily routines, and any changes in sleep resulting from the activities.

### Statistical Analyses

Siblings in the same family may wish to participate, and they would be convenient participants, given their familiarity with the intensive intervention protocols. However, siblings represent family clustering that must be statistically accounted for. We examined the intraclass correlation coefficient (ICC) for families in our recent observational repeated-measures study of screen use and sleep in teens [73], which was low (ICC=0.005). Using this ICC and an average family cluster size of 2, the design effect is 1.005 [74], which has a negligible effect on the required sample size (60*1.005=60.3). Therefore, siblings may be recruited but will be assessed at different times throughout the year, will be individually randomized, and will contribute to no more than half the sample (ie, n=36 participants must not have siblings in the study).

Primary statistical analyses will be undertaken using data from adherent days; secondary analyses will use all data. Mixed effects regression models with a random effect for participants nested within a family cluster will be used to estimate mean differences, 95% CI, and *P* values for conditions 2, 3, and 4 compared with condition 1. Residuals will be plotted and visually assessed for homoskedasticity and normality. Adjustments for within-person confounding (eg, lunar phases) will be undertaken as sensitivity analyses. Results will be reported in line with the CONSORT (Consolidated Standards of Reporting Trials) statement extension to crossover trials. Descriptive analyses will also be undertaken to explore participants’ experiences with the interventions as well as their adherence. Relationships between sleep and quality of life measures will be assessed using repeated measures mixed effects analyses.

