**Methods:**

After a baseline week to assess usual behavior, 72 children (10-14.9 years old) will be randomized to four conditions, which are (1) avoid all 3 behaviors, (2) use screens for at least 30 minutes, (3) be physically active for at least 30 minutes, and (4) eat a large meal, during the hour before bed on days 5 to 7 of weeks 2 to 5. Families can choose which days of the week they undertake the intervention, but they must be the same days for each intervention week. Guidance on how to undertake each intervention will be provided. Interventions will only be undertaken during the school term to avoid known changes in sleep during school holidays. Intervention adherence and shuteye latency (time from getting into bed until attempting sleep) will be measured by wearable and stationary PatrolEyes video cameras (StuntCams). Sleep (total sleep time, sleep onset, and wake after sleep onset) will be measured using actigraphy (baseline, days 5 to 7 of each intervention week). Mixed effects regression models with a random effect for participants will be used to estimate mean differences (95% CI) for conditions 2 to 4 compared with condition 1.

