## Methods

### Study Design

The helpful activities before it is time to sleep (HABITS) study is a randomized crossover trial to experimentally determine whether banning electronic media, physical activity, or food intake in the hour before bed actually impact children’s sleep quantity and quality. Wearable cameras will be used to obtain objective measures of prebed behaviors and accelerometers for objective measures of sleep. The study will be conducted in participants’ homes and at the University of Otago in Dunedin, New Zealand.

All children will undergo a baseline week to establish usual prebedtime behavior and set bedtimes for the intervention weeks. Each participant will follow 4 experimental prebedtime conditions in a randomized order (Figure 1). The comparison or ideal week will be condition A. In condition B (screens week), participants can use any device and undertake any screen behavior. In condition C (exercise week), suitable options will be suggested for both indoor (eg, wrestling and dancing) and outdoor (tag, sports, and walking) activities. In condition D (food week), participants will be asked to eat a large meal in the hour before bed.

Families will follow each intervention condition on the same consecutive 3 days of each intervention week (days 5-7). In total, 3 days will provide sufficient data to determine how each behavior influences sleep, allows a washout between each condition, and is a pragmatic choice to limit participant or researcher burden. As we are examining the effect of the condition on sleep the same night, this amounts to 3 observations/participant/condition, which should give more reliable estimates than 1 observation or condition. Each family can choose what days of the week are days 5-7 for them, as long as the same days apply across all 5 weeks. All interventions will occur during the school term to limit known changes in sleep caused by holidays [58]. Daylight savings will be avoided and lunar patterns will be recorded to examine the potential for confounding across the different phases.

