### Sample Size

To detect a difference of 15 minutes (assuming within-person SD of 35 minutes) in TST [60], with 90% power at a .05 α level, a sample size of 60 participants would be required. We will recruit 72 children, allowing for 20% nonadherence, dropout, or incomplete data.

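### The stated night-level model has no participant-by-week term, so standard errors for TST and other nightly outcomes may be too small if nights in the same condition week are correlated

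*Protocol article*

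**What the plan says.** The random part of the model is stated twice. Statistical Analyses has "Mixed effects regression models with a random effect for participants nested within a family cluster will be used to estimate mean differences". The abstract's Methods paragraph names the participant level only: "Mixed effects regression models with a random effect for participants will be used to estimate mean differences (95% CI".

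The unit of analysis is the night: "Primary statistical analyses will be undertaken using data from adherent days; secondary analyses will use all data".

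The unit to which condition is assigned is the week. Study Design states: "Families will follow each intervention condition on the same consecutive 3 days of each intervention week (days 5-7". Each child meets each condition in one week only, so participant-by-week and participant-by-condition are the same level.

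The only clustering that Statistical Analyses discusses is between siblings, with a family ICC of 0.005 and a design effect of 1.005. It mentions no participant-by-week term, residual correlation, robust standard error or week-level summary.

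**The concern.** A random intercept for child, or for child within family, removes only what is constant over all 12 intervention nights. Anything specific to one child's week stays in the three nights of that week together: illness, school events, accumulated sleep debt, or how that child responds to that condition. The Discussion itself expects families to differ in how they carry out the meal and exercise conditions, and Study Design plans to look for confounding between phases.

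In the stated model this shared variation is pooled with night-to-night noise and treated as if it averaged out over three nights. It does not, because all three nights carry the same week-level deviation. If that variance is appreciable, confidence intervals for the three contrasts against condition A are too narrow and P values too small, for the primary outcome and for every outcome measured nightly. Outcomes collected once per week (PROMIS sleep impairment, KIDSCREEN) are not affected. The trial is meant to inform sleep guidelines and its authors expect limited effects, so false positive contrasts would matter.

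**Working it through.** **Inputs.** From Sample Size: "To detect a difference of 15 minutes (assuming within-person SD of 35 minutes) in TST", and "with 90% power at a .05 α level, a sample size of 60 participants would be required". From Study Design: 4 conditions, 3 nights each. Assumed, because the article gives no value: ρ, the share of within-child nightly variance that lies between a child's weeks, and δ, the share that lies between that child's weekdays. A two-sided test is also assumed.

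**The plan's own figure.** With 35 minutes as the SD of one within-child difference, the normal approximation gives n = [35 × (1.960 + 1.282) / 15]² = 57.2, so 58. A paired t calculation gives 60, with power 0.904. The stated 60 is therefore reproduced by one difference per child. Three independent nights with a nightly SD of 35 would give 41.

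**Expected mean squares.** Take N = 60 and scale the within-child nightly variance to 1, with night-level residual e = 1 − ρ − δ.

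- Participant-by-week: 3(N − 1) = 177 df, expectation 3ρ + e
- Participant-by-weekday: 2N = 120 df, expectation 4δ + e
- Remainder: 6N = 360 df, expectation e

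The stated model pools all 657 df into one residual M. The contrast between two conditions actually has error T = 3ρ + e. With V the nightly variance, the model SE is √(2MV/3N) and the correct SE is √(2TV/3N), so their ratio is √(M/T). The type I error of a nominal 5% test is 2[1 − Φ(1.96 × ratio)]. The ratio does not depend on V.

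**Worked case, ρ = 0.3, δ = 0.** T = 0.9 + 0.7 = 1.6. M = (177 × 1.6 + 480 × 0.7)/657 = 0.9425. Ratio = √(0.9425/1.6) = 0.767. Type I error = 2[1 − Φ(1.504)] = 0.133.

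**No weekday variance (δ = 0).** The SEs in minutes take 35 as a nightly SD.

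| ρ | model SE | correct SE | ratio | type I error |
|---|---|---|---|---|
| 0 | 3.69 | 3.69 | 1.00 | 5.0% |
| 0.05 | 3.67 | 3.87 | 0.95 | 6.3% |
| 0.1 | 3.65 | 4.04 | 0.90 | 7.6% |
| 0.2 | 3.62 | 4.37 | 0.83 | 10.4% |
| 0.3 | 3.58 | 4.67 | 0.77 | 13.3% |
| 0.5 | 3.51 | 5.22 | 0.67 | 18.8% |

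Simulating 20,000 null trials each at ρ = 0, 0.1, 0.2, 0.3 and 0.5 gave 5.0%, 7.6%, 10.4%, 13.6% and 18.8%. Analysing one mean per child per condition, with complete nights, held 4.9% to 5.0% throughout.

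**Weekday variance (δ = 0.2).** Each child repeats the same weekdays, so this component enters M but cancels from the contrast. At ρ = 0.05, T = 0.90 and M = (177 × 0.90 + 120 × 1.55 + 360 × 0.75)/657 = 0.937, giving ratio 1.02 and type I error 4.6%. At ρ = 0.1 the error is 5.9%, and at ρ = 0.2 it is 8.8%. Setting M = T gives 120 × 4δ = 480 × 3ρ, so the two errors cancel exactly when δ = 3ρ.

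**Two adherent nights per week (δ = 0).** Now T = 1 + ρ, with 177 df at week level and 240 df below it. The type I error is 6.4%, 7.8% and 9.3% at ρ = 0.1, 0.2 and 0.3.

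**The case against.** **The damage is conditional.** A reader might infer that the standard errors are too small as a matter of fact. The article does not support that. It gives no within-week correlation, and at ρ = 0 the stated model is correct.

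**The design contains an offset.** Every child uses the same weekdays each week, and the Randomization section holds bedtime fixed for a given weekday across the four intervention weeks. If child-by-weekday differences are large relative to week-level variance, the stated model is correct or even conservative. This stands. At small ρ the direction of the error is not settled.

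**Three complete nights is the upper case.** The primary analysis keeps adherent nights only, and with two per week the inflation is smaller. This stands too.

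**The reliability sentence.** A reader might also fault Study Design for saying "this amounts to 3 observations/participant/condition, which should give more reliable estimates than 1 observation or condition". It is not an error. A three-night mean is more precise than one night for any ρ below 1 (at ρ = 0.3 its variance is (1 + 2 × 0.3)/3 = 0.53 of a single night's), and the sentence does not claim independence.

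**Level of detail.** A condensed article may leave the covariance structure to an analysis plan that is not shown and might add this level. But the article does not leave the point open. It names the random effects, discusses clustering for siblings alone, and the model it states lacks the level at which condition is assigned.

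**Conclusion.** The point holds in conditional form. The stated model omits participant-by-week variance. If that variance is positive and not offset, standard errors for the nightly contrasts are too small. With 60 children and three nights per week, type I error runs from 5% at ρ = 0 to about 19% at ρ = 0.5 without weekday variance, and is lower with weekday variance or fewer adherent nights. The missing term is certain; the size of its effect rests on assumed correlations.

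A reader might go on to infer that the trial is too small. The calculation does not show that. The figure of 60 is reproduced by one difference per child and does not rely on independent nights. If 35 minutes is instead a nightly SD, a correct three-night analysis needs 41 children at ρ = 0, 60 at ρ = 0.25 and 79 at ρ = 0.5, and the article does not settle which case applies.

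This should be corrected before analysis. It does not undermine the design.

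**What to change.** Add a random intercept for participant-by-week (the condition period), nested in participant within family, with Kenward-Roger or Satterthwaite degrees of freedom, for TST and every other nightly outcome. Consider a participant-by-weekday random intercept as well, since the same weekdays recur, and report the estimated variance components.

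Participant-week means are only an approximate fallback. They match the nested model when every week contributes the same number of nights, but selecting adherent nights will make the counts unequal, and unweighted means would treat one-night and three-night weeks alike.

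The cost is one or two model terms and no new data. Intervals may be somewhat wider; if the week-level variance is close to zero they will hardly change.

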### Randomization

#### Overview

Once the baseline appointment is completed, participants will be randomized using the REDCap (Research Electronic Data Capture; Vanderbilt University) randomization module [63] to one of 4 intervention group orders using a computer-generated sequence, stratified by age (from 10 to less than 13 years or from 13 to 15 years), with random block sizes of 4 or 8. The 4 group orders are from a Williams Latin square balanced for first-order carryover effects. Usual bedtimes will be discussed with families, based on camera footage from baseline. While bedtime for each night of intervention (ie, nights 5-7 of each intervention week) can be different, each day of the week must be consistent between all 4 intervention weeks.

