### Intervention Adherence

Objective and subjective measures will be used to assess adherence. On days 5-7 of each intervention week, participants will wear a PatrolEyes Max (StuntCams) camera on a chest harness from 90 minutes before bedtime until bedtime. These cameras (weighing 160 g and having dimensions 79×57×27 mm) provide time-stamped footage, face outwards, record audio and video (including overnight use through infrared), and quantify when and how much screen use has occurred [65]. We will also be able to determine when and what food or beverages were consumed, supplemented with a brief questionnaire (text message) on mornings 6, 7, and 8, asking them whether they consumed any food or drinks in the hour before bed last night, as well as any caffeine intake. We will use the wearable cameras to code for moderate-to-vigorous physical activity (Compendium of Physical Activity metabolic equivalent values >4 [66]) using a reliable video coding protocol that codes free-living physical activity behavior, supplemented with information from heart rate monitors and accelerometers. Since the wearable cameras can be removed before bedtime (eg, bathing), a second stationary camera will be set up in the participant’s bedroom 10 minutes before bedtime. This “back-up” camera would detect any time-stamp missing from the wearable camera (as long as the participant is in their bedroom) and is also used to assess some aspects of sleep (more details are discussed in the *Sleep* section). It will not be possible to blind coders (as they are looking for specific behaviors) or participants (as they know what behaviors they need to do), but statistical analysis will be undertaken blinded to the intervention order.

The following predefined cut-offs will be used to classify participants as “adherent” for the per-protocol analysis (ie, those who followed the HABITS protocol):

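### The primary model as described leaves out period and night of week; intervals are slightly wide with all nights kept, and contrasts on adherent days can be biased under some adherence patterns

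*Protocol article*

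**What the plan says.** All references are to the protocol article.

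- **Model** (Statistical Analyses): "Mixed effects regression models with a random effect for participants nested within a family cluster will be used to estimate mean differences", for conditions 2, 3 and 4 against condition 1. No other fixed effect is named.
- **Other adjustment** (same section): "Adjustments for within-person confounding (eg, lunar phases) will be undertaken as sensitivity analyses".
- **Analysis set** (same section): "Primary statistical analyses will be undertaken using data from adherent days; secondary analyses will use all data". The adherence rules under Intervention Adherence differ by condition: A must avoid all three behaviours, while B, C and D each require one and restrict the other two.
- **Design** (Randomization): "The 4 group orders are from a Williams Latin square balanced for first-order carryover effects", stratified by age, "with random block sizes of 4 or 8". Bedtime may differ between nights, but for a given day of the week it is held the same across the four intervention weeks.
- **Nights** (Study Design): "Each family can choose what days of the week are days 5-7 for them", provided that the days are the same in all five weeks; "this amounts to 3 observations/participant/condition".
- **Blinding** (Intervention Adherence): "statistical analysis will be undertaken blinded to the intervention order".

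**The concern.** The design balances condition over week by the Williams square, and over night of the week by holding each child's three days fixed. A model that uses neither factor leaves any week or night effect in the residual. With every night present, balance protects the point estimates and only precision suffers. The primary analysis then removes nights by rules that differ between conditions, so nothing guarantees that the retained nights are still balanced. If they are not, a drift over the weeks, or a difference between school and free nights, can enter the condition contrasts.

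The Discussion says the authors expect limited effects, so small contrasts will be interpreted and a shift of a few minutes would matter. The blinding sentence adds a practical difficulty: week together with condition is the order, so an analyst kept from the order, read literally, could not be given both.

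**Working it through.** **Inputs from the protocol article.** Target difference 15 min, within-person SD 35 min, 90% power, alpha .05 (taken as two-sided), 60 children (Sample Size); four orders by four weeks, three nights per condition (Randomization, Study Design).

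**Assumed, because the documents give no figures.** 35 min is the residual SD of a single night; between-child SD 40 min; drift 5 or 10 min per week; third night longer by 15 or 30 min for every child; retention rates as listed below. A standard Williams square is used with 15 children per order.

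**Step 1: the plan's own figure.** n = (SD × (z₀.₉₇₅ + z₀.₉₀) / difference)² = (35 × (1.960 + 1.282) / 15)² = 57.2, so 58 by the normal approximation. The paired t calculation gives 60, with power 90.4%. The stated 60 reproduces with 35 as the SD of a paired difference.

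**Step 2: all nights kept.** There are 60 × 12 = 720 nights. SE of a contrast = √(2s²/180). With s² = 35² = 1225 this is 3.69. Omitting the effects adds their variance × 720/657 to s², where 657 = 720 − 60 − 3.

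- 5 min/week: values 0, 5, 10, 15 have variance 31.25, which adds 34.2.
- 10 min/week: variance 125, which adds 137.0.
- 5 min/week and third night +30: 31.25 + 200 = 231.25, which adds 253.4.

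Simulation (1000 trials per scenario, no true condition effect) agrees:

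| Assumed effect | SE by hand, no terms | Simulated model SE, no terms | Simulated model SE, with terms | Excess width | Coverage, no terms |
|---|---|---|---|---|---|
| 5 min/week | 3.74 | 3.74 | 3.68 | 2% | 95.6–96.0% |
| 10 min/week | 3.89 | 3.90 | 3.69 | 6% | 95.6–97.1% |
| 5 min/week, +30 night | 4.05 | 4.06 | 3.68 | 10% | 97.0–97.2% |

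Mean bias was 0.2 min or less throughout.

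**Step 3: nights dropped.** A rough size for the bias is the difference between conditions in the mix of retained weeks or nights, multiplied by the week or night effect.

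- *Retention by condition only* (A 60%, B 85%, C 60%, D 75%; 5 min/week, +30 night). Every condition keeps the same mix, so the expected shift is zero. Simulated: 0.21 to 0.34 min, with simulation error about 4.9/√1000 = 0.15 per contrast. Multiplying these rates by a common weekly factor (5 min/week, no night effect) gave 0.06 to 0.14 min.
- *Retention in A falling 85, 70, 55, 40% over the weeks, the others constant.* Mean week index in A = (0.70 + 2 × 0.55 + 3 × 0.40) / 2.50 = 1.20, against 1.50 elsewhere. Shift = 0.30 × 5 = 1.5 or 0.30 × 10 = 3.0 min. Simulated: about 1.7 min (coverage 93–94%) and 3.1 to 3.3 min (90–91%).
- *Third-night retention A 40%, B 95%, C 50%, D 60%; other nights 80%.* The third night's share is 0.40/2.00 = 0.200 in A and 0.95/2.55 = 0.373 in B. Shift for B against A = 0.173 × 15 = 2.6 or 0.173 × 30 = 5.2 min. Simulated: 2.6 min (coverage 91%) and 5.5 min (80%). C and D against A moved less: 0.8 to 1.1 min at +15 and 1.1 to 2.2 min at +30.

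With period and night terms in the model, bias in the last two patterns was within 0.2 min and coverage was 94–96%.

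**The case against.** The strongest reply is that the article is condensed, that an unseen analysis plan may list period and night as fixed effects, and that reporting will follow the CONSORT crossover extension. This stands in part: the article does not say that the terms are excluded, and a reader who infers that they are goes beyond the text. But the article does place adjustment for within-person factors among the sensitivity analyses. Week and night vary within a child, so as written they fall there and not in the primary model. Lunar phase is given only as an example, so it would be unfair to say that the plan adjusts for the moon and ignores the calendar.

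A reader might also infer three stronger things that the documents do not support:

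- *That blinding to order prevents a period term.* It does not: week number can be supplied with condition labels masked. Children are randomized to orders, so the sentence may simply mean blinding to allocation. It needs clarifying.
- *That the intervals are simply wrong.* With complete nights they are mildly conservative, and only if week or night effects exist.
- *That dropping nights necessarily biases the contrasts.* It does not, as the condition-only pattern shows. Bias through week or night needs a real effect of that factor, and retention that depends jointly on condition and that factor.

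The design also limits the problem. The trial runs in term time with fixed days and bedtimes. A child who uses the Monday to Wednesday example under Recruitment and Eligibility contributes no mix of school and free nights. The night scenarios above give every child a different third night, so they lean towards the large side. Finally, making adherent days primary is the deeper source of the risk, and that is a separate question.

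**Conclusion.** The point holds in limited form. As described, the primary model does not use two factors that the design deliberately balances, and the primary analysis set can undo that balance. With all nights kept, the cost is about 2 to 10% in interval width and no bias. On adherent days, the worst-affected contrast can be off by about 1.7 to 5.5 minutes, or 11 to 37% of the 15-minute target (1.7/15 and 5.5/15), with coverage down to about 80% in the harshest case. Those figures rest on assumed drift, night effects and retention; the direction of any bias depends on which nights are lost.

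The terms have limits. They do not remove selection on other causes of non-adherence, nor do they handle correlation between nights of the same child and week. With an assumed child-by-week SD of 15 min, the model SE was 3.95 against an actual spread of about 4.6, and coverage was about 90–92% with or without the terms.

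**What to change.** In Statistical Analyses, name fixed effects for period (weeks 2 to 5) and for night (day of the week, or school against non-school night) in the primary model, and use the same model in the all-data analysis. Keep lunar phase and similar factors as sensitivity analyses.

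In Intervention Adherence, replace the blinding wording by a statement that the analyst receives week, night and a coded condition label, unmasked once the model is fixed.

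Both variables follow from the study schedule, so no new data are needed. The cost is 3 degrees of freedom for period plus 1 for night type (up to 6 for day of the week), out of 720 nights if 60 children complete, and one rewritten sentence.
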